#### Aim 2—Heterogeneity of Treatment Effect

An essential part of patient-centered care is recognizing that not all patients will respond to treatments the same way. As such, exploratory, hypothesis-generating heterogeneity of treatment effect (HTE) analyses will be conducted to identify patient-level factors associated with treatment response to either MT or CBT by incorporating 6 relevant variables (sex, race, ethnicity, education, outcome expectancy, and time since cancer diagnosis) and variable-by-intervention interaction terms in the mixed-effects model described above in the *Aim 1—Hypotheses 1(a) and 1(b)* section. These 5 exploratory LMM-based analyses will be guarded against inflated type I error owing to multiple testing by adjusting the variable-by-intervention interaction *P* values for the false discovery rate [143,144]. This type of subgroup analysis, although patient centered, may need to be interpreted with caution and cannot replace the primary analyses. The evaluation and reporting of HTE analyses will be based on the approach proposed by Kent et al [145]. However, recognizing other factors may also contribute to treatment responses, the study team will also apply Bayesian [146,147] and machine learning [148,149] methods, which can identify HTE and subgroups based on multiple variables simultaneously and are potentially more powerful than traditional univariate methods.

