### The Music Therapy Versus Cognitive Behavioral Therapy for Cancer-Related Anxiety Trial: Study Aims and Hypotheses

The Music Therapy Versus Cognitive Behavioral Therapy for Cancer-related Anxiety (MELODY) trial seeks to address the following aims:

The primary aim is to determine the comparative effectiveness of telehealth-based MT versus telehealth-based CBT for anxiety and comorbid symptoms in cancer survivors.

*Hypothesis 1(a)*: MT will be noninferior to CBT in treating anxiety symptoms among survivors at week 8 (end of treatment) and week 26 (long-term follow-up).*Hypothesis 1(b)*: Compared with CBT, MT will be associated with significantly greater improvement in fatigue co-occurring with anxiety.Exploratory hypothesis: Survivors may have unique experiences with MT and CBT for anxiety during cancer survivorship.

The secondary aim is to identify patient-level factors associated with greater anxiety symptom reduction after MT and CBT.

*Hypothesis 2*: Specific sociodemographic characteristics (eg, age, sex, race, and education) or psychological attributes (ie, expectancy) will be associated with treatment response to MT or CBT.

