### Analytical Approach

#### General Description

Analyses will be conducted using the intention-to-treat principle (ie, participants will be analyzed according to their randomly assigned treatment group regardless of dropout or treatment adherence status). Given that CBT is widely recognized as a first-line therapy for anxiety, the study team opted to test the noninferiority of MT to CBT, with the goal of understanding whether MT can be an appropriate treatment option for patients who lack CBT access or do not wish to pursue CBT. To provide complementary information for treatment decision-making, the study team will also test which intervention is superior for addressing fatigue and other symptoms co-occurring with anxiety. For all specific aims, the main analytical tool will be a linear mixed-effects model (LMM) because the primary outcome (anxiety) and secondary outcomes (fatigue, depression, insomnia, pain, cognitive dysfunction, and health-related quality of life) are repeated continuous outcomes over time [142]. This statistical procedure takes into account within-subject correlations from repeated measurements in the same subjects and allows the estimation of between-group differences without necessitating the exclusion of participants with missing data. The general template of each LMM will model the outcome as a function of the treatment arm and assessment time (categorical), controlling for the randomization stratification variables (baseline anxiety medication use, preferred language, and study site) and including a subject-specific random intercept. The general LMM template will be tailored to test the specific aim hypotheses by adding interaction terms (eg, time-by-intervention) and additional covariates of interest to the model and by reparametrizing the assessment time variable to focus on specific contrasts.

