#### Aim 1—Hypotheses 1(a) and 1(b)

Outcome measure trajectories will be plotted by randomization arm over time. Each outcome measure will be summarized at each assessment time by treatment arm using descriptive statistics. Comparisons between randomization arms with respect to changes in symptom outcomes will be based on specific coefficients from time-by-arm interactions added to the general LMM template described above in the *General Description* section. Specifically, the model will include all time points (categorical) at which the outcome was assessed (baseline and weeks 4, 8, 16, and 26), and the time-by-arm interaction will include multiple coefficients corresponding to the time-by-arm interaction at each discrete postbaseline time point. However, statistical inferences will focus on the interaction coefficients at 8 and 26 weeks, which are interpreted as the differences between arms in change from baseline to 8 and 26 weeks, respectively. For hypothesis 1(a), the 2 primary end points are HADS anxiety score changes at 8 weeks and 26 weeks. On the basis of the LMM coefficients for the time-by-arm interaction at weeks 8 and 26, 2 tests will be performed to determine whether MT is noninferior to CBT at reducing the HADS anxiety subscale score within a noninferiority margin of 0.35 SD for both comparisons. The noninferiority of MT to CBT will be tested at a significance threshold of *P*<.025 for each comparison, controlling the overall type I error at *P*=.05 for the primary end point comparisons. For hypothesis 1(b), a similar LMM evaluating BFI scores over time will be used to test whether the MT arm had significantly greater improvement in fatigue (BFI score) compared with the CBT arm at weeks 8 and 26. In contrast to the primary end point noninferiority comparisons, these tests will be superiority tests. For other comorbid symptoms (eg, depression and insomnia) and quality of life, the methods described for hypothesis 1(b) will be used to compare the treatment arms. Given that a small number of cancer survivors may experience disease recurrence during the 26-week study, sensitivity analyses will be performed, excluding those individuals who experienced a recurrence during the study period. These sensitivity analyses will not replace the primary analysis.

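### Aim 2 names a two-way variable-by-intervention term that, read literally, averages over all five visits including baseline instead of targeting change to weeks 8 and 26, and it counts six variables as 5 analyses

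*Protocol article*

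**What the plan says.** The secondary aim (Study Aims and Hypotheses) is to find patient-level factors that go with a larger reduction in anxiety. Hypothesis 2 gives its candidates as "Specific sociodemographic characteristics (eg, age, sex, race, and education"), plus expectancy.

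The Aim 2 section sets the analysis: "6 relevant variables (sex, race, ethnicity, education, outcome expectancy, and time since cancer diagnosis) and variable-by-intervention interaction terms in the mixed-effects model" described for Aim 1. It then says "These 5 exploratory LMM-based analyses will be guarded against inflated type I error" by an FDR adjustment, and the P values it names for that adjustment are those of the variable-by-intervention terms. No time point is given for Aim 2.

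The Aim 1 section defines the model being reused: "the model will include all time points (categorical) at which the outcome was assessed (baseline and weeks 4, 8, 16, and 26"). The arm comparison rests on the time-by-arm coefficients at weeks 8 and 26, "which are interpreted as the differences between arms in change from baseline to 8 and 26 weeks, respectively".

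The General Description specifies a subject-specific random intercept. It allows the template to be tailored for each aim by "adding interaction terms (eg, time-by-intervention) and additional covariates of interest to the model and by reparametrizing the assessment time variable".

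**The concern.** In a model with baseline among the outcome rows, the treatment effect on change is the arm-by-time coefficient, not the arm coefficient. To ask whether a variable modifies that effect, the variable has to interact with arm-by-time. A variable-by-arm term with no time in it describes a difference held constant over every visit, including the one before treatment. The term that is named, and whose P value is to be adjusted, therefore does not line up with the aim. If it is fitted as written, the reported coefficient understates modification at weeks 8 and 26, and it takes in any chance subgroup-by-arm difference already present at baseline.

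Separately, an FDR adjustment needs a defined family of tests. Six variables and 5 analyses in consecutive sentences leave the family unclear. Age appears in the hypothesis but not in the list of variables.

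**Working it through.** **Inputs from the protocol article.** Five visits (baseline, weeks 4, 8, 16, 26) and a random intercept; 150 per arm with 15% attrition, so 150 × 0.85 = 127.5 evaluable per arm; SD of the HADS anxiety score 4.2.

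**Assumptions not in the article.** Complete data for 128 per arm; a two-level moderator split 50/50, so 64 per arm-by-moderator cell; within-person correlation r of 0.3, 0.5 or 0.7; an illustrative modification of 3 points; two-sided 0.05 before FDR adjustment.

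**The plan's own figure.** No power is stated for Aim 2. The stated 80% for the primary tests reproduces: 0.35/√(2/127.5) = 2.79, and Φ(2.79 − 1.96) = 79.8%. The evaluable number is therefore a sound base for what follows.

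**What the two-way coefficient estimates.** Let d_t be the modification at visit t, where d_0 is the baseline difference (zero in expectation under randomization). With complete data and a random intercept, the coefficient is a contrast of participants' five-visit means:

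coefficient = (d_0 + d_4 + d_8 + d_16 + d_26)/5

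- Equal modification d at all four post-baseline visits: (0+1+1+1+1)/5 = 0.8 d
- Only at weeks 8 and 26: (0+0+1+0+1)/5 = 0.4 d
- Only at one of those weeks: 1/5 = 0.2 d
- +d at week 8 and −d at week 26: 0
- A constant subgroup-by-arm difference already there at baseline, with no modification of change: 5/5 = 1.0 of that difference

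The three-way coefficients at weeks 8 and 26 recover d in full in the first four patterns (at the weeks where it is present) and give 0 in the last. An exact generalized-least-squares calculation of both models gave the same values.

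**Standard errors.** With four cells of 64:

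- Two-way: √[4 × 4.2² × (1+4r)/5 / 64] = 0.696, 0.813, 0.915 for r = 0.3, 0.5, 0.7
- Three-way at one week: √[4 × 2 × 4.2² × (1−r) / 64] = 1.242, 1.050, 0.813

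**Power for a 3-point modification (r = 0.3 / 0.5 / 0.7).**

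| Modification present at | Two-way coefficient | Two-way power | Three-way power, week 8 |
|---|---|---|---|
| Weeks 4, 8, 16 and 26 | 2.4 | 93% / 84% / 75% | 68% / 82% / 96% |
| Weeks 8 and 26 only | 1.2 | 41% / 31% / 26% | 68% / 82% / 96% |
| Week 8 only | 0.6 | 14% / 11% / 10% | 68% / 82% / 96% |

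Example for the second row at r = 0.5: two-way Φ(1.2/0.813 − 1.96) = 31%; three-way Φ(3/1.050 − 1.96) = 82%.

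**The FDR family.** At an assumed 5% FDR, the smallest Benjamini-Hochberg threshold is 0.05/5 = 0.0100 for the stated 5 analyses, 0.05/6 = 0.0083 for six variables at one week, and 0.05/12 = 0.0042 for six variables at both weeks.

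**The case against.** The General Description expressly permits extra interactions and a reparametrized time variable for every aim, and in a condensed article variable-by-intervention may be shorthand for modification of the week 8 and week 26 effects. A reader might infer that the wrong model will be fitted; the text does not prove that. What stands is that the general permission does not select a term. The Aim 2 section does select one, twice, and it is not the one that matches the aim.

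A reader might also infer that the two-way test is invalid or says nothing about who improves more. That goes too far. The moderators are baseline variables and treatment is randomized, so the expected baseline variable-by-arm difference is zero, and chance imbalance is already reflected in the standard error. The test of no modification remains valid. Nor is it always weaker: with equal modification at all post-baseline visits it has the higher power at correlations 0.3 and 0.5. The objection is to its target, not its validity.

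On the counts, an FDR procedure runs on the P values actually produced, so the miscount has little practical effect. The Covariates section writes race or ethnicity as one item, which could explain 5, but the Aim 2 section lists them separately and says six.

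On age, one might infer that a stated hypothesis goes untested. Age is only an example there, the other sociodemographic examples and expectancy are on the Aim 2 list, and the planned Bayesian and machine-learning analyses may take in other factors. It is an inconsistency, not a contradiction.

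**Conclusion.** The point holds in a limited form. The Aim 2 test as named does not target modification of anxiety reduction at weeks 8 and 26. Read literally, it returns between 0.2 and 0.8 of the modification in the one-directional patterns examined, and nothing if the two weeks go in opposite directions. The fractions rest on complete data and a random intercept; attrition would change the visit weights. The powers also rest on the assumed correlation, the 50/50 moderator and the 3-point effect.

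The mismatch between six variables and 5 analyses is a plain internal contradiction with a small consequence. The omission of age is an inconsistency to reconcile.

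The primary noninferiority analysis and its power are untouched, and the article labels Aim 2 exploratory and hypothesis-generating. The correction is still worth making, because this is the declared secondary aim and a change of wording settles it.

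**What to change.** - State that Aim 2 tests the variable-by-time-by-intervention terms at weeks 8 and 26, with the lower-order variable-by-time terms also in the model. For a variable with more than two levels, use one joint test per week.
- Make the stated count equal the tests actually performed: 6 if one week is tested, 12 if both are. If race and ethnicity are meant as one variable, say so and change the six to match.
- Either add age to the Aim 2 list, which makes 7 variables (14 tests at two weeks with one test per variable per week), or remove it from the examples in Hypothesis 2.

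The cost is wording and a slightly stricter FDR threshold. No new data are needed: age is already collected at baseline. Where modification is constant after baseline and within-person correlation is low, the week-specific test gives up some power compared with the averaged one; that is the price of answering the question the aim asks.

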#### Qualitative Analyses

All interviews will be transcribed verbatim and imported into MAXQDA 2022 (VERBI Software) for analysis. The semistructured interviews will be analyzed using theoretical thematic analysis procedures as per the guidelines by Braun and Clarke [150,151]. Such an analysis is aimed at identifying patterns driven by an a priori theoretical framework or research questions. Themes will be identified using a semantic approach in which themes are derived from “the explicit meaning of the data and the analyst is not looking for anything beyond what a participant has said” [150]. Two coders will code the interview transcripts. To ensure the trustworthiness of the analysis, the primary coder will code each transcript, whereas the secondary coder will code 30% of the transcripts. Coding discrepancies will be resolved through discussion until consensus is reached. The codes will then be organized into categories, reviewed, and subsequentially organized into broader themes. Interviews from each treatment arm will be analyzed separately and then compared for convergence and divergence. The themes will be linked to patient-reported outcomes to explore whether specific themes vary according to the magnitude of change in the HADS anxiety score. To augment the HTE analyses, the study team will also explore whether qualitative themes differed by subgroup (eg, sex, race, ethnicity, education, outcome expectancy, and time since cancer diagnosis) within each treatment group.

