### Eligibility Criteria

The eligibility criteria were designed to be broad and consistent with a pragmatic design while ensuring participant safety and scientific rigor. Participants are eligible if they are English- or Spanish-speaking, are aged ≥18 years, have a prior cancer diagnosis of any type or stage, are free of oncological disease, have a score of ≥8 on the anxiety subscale of the Hospital Anxiety and Depression Scale (HADS), report anxiety symptoms lasting at least 1 month, and have access to Zoom and a quiet or private location. Participants will be excluded if they had completed active cancer treatment (eg, surgery, radiation, and chemotherapy) less than 1 month before enrollment; however, participants receiving maintenance hormonal or targeted therapies will be allowed to enroll. Participants will also be excluded if they have active suicidal ideation, bipolar disorder, schizophrenia, or substance abuse; have a score of ≥10 indicative of cognitive impairment on the Blessed Orientation-Memory-Concentration; or received a treatment course of ≥7 MT or CBT sessions for anxiety symptoms within the last 6 months.

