#### Anxiety

The primary outcome is severity of anxiety symptoms, as assessed using the HADS anxiety subscale. The reliability, validity, and factor structure of this 7-item subscale has been established in patients with cancer with a Cronbach α of .83 [118,119]. A score of ≥8 indicates the presence of anxiety symptoms. Research has identified a minimal clinically important difference (MCID) of 1.7 points [120]. The HADS anxiety subscale will be administered at baseline and at weeks 4, 8, 16, and 26.

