#### Semistructured Interviews

It may be difficult to capture the impact of MT and CBT using quantitative measures alone. Methodological experts recommend mixed methods approaches to understand patient experiences with health interventions [139-141]. Thus, qualitative method specialists will conduct 45-minute, semistructured individual interviews over the phone at week 8 (end of treatment). To reach thematic saturation from interviews, the research team will purposively sample 30 survivors in each treatment arm to be interviewed (N=60), aiming for balance across age, sex, race, ethnicity, and treatment response. Interviews will be conducted shortly after the intervention period to enhance the recall of personal experiences during therapy sessions. Interviews will be conducted using a semistructured guide that covers the following topics: (1) acceptability: treatment satisfaction, usefulness of the intervention, barriers and facilitators to session attendance, and adherence to and engagement with between-session assignments; (2) impact on anxiety symptoms and coping: perceived benefits and harms of the intervention on anxiety and comorbid symptoms, how one copes with stress and anxiety, integration of learned skills into daily life, and plans for maintaining anxiety management skills; (3) digital literacy and experience: views toward technology, comfort level with telehealth, and transfer of acquired digital skills to other aspects of daily living; and (4) unexpected experiences: unanticipated benefits, harms, or insights from engaging with the interventions. The interview guide will include flexibility in asking probing questions to enable participants to elaborate on their experiences. All the interviews will be audio-recorded and transcribed for thematic analysis.

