#### Sample Size and Power

The sample size is based on the primary hypothesis that MT is noninferior to CBT for anxiety reduction at weeks 8 and 26. Two tests will be performed to determine whether MT is noninferior to CBT at reducing HADS anxiety at weeks 8 and 26, each with a noninferiority margin of Cohen *d*=0.35 SD for both comparisons. These comparisons will be based on the LMM coefficients for the time-by-arm interaction at weeks 8 and 26; however, the power calculation is based on 2-sample *t* tests of differences between the arms in their change scores. Therefore, the power estimate is conservative, that is, in the LMM-based analysis, there will be slightly higher power than the power calculation presented below, with all other assumptions held constant. Assuming 150 participants are randomized to each arm, 15% attrition, and a 1-sided significance threshold of *P*=.025 (controlling the overall type I error at 0.05 for our 2 primary end point comparisons), there will be 80% power to find MT noninferior to CBT with respect to the HADS anxiety subscale scores at weeks 8 and 26 within a noninferiority margin of Cohen *d*=0.35 SD.

The noninferiority margin was informed by a large study that used multiple rigorous methods to empirically estimate a difference of 1.7 points as the MCID for the HADS scales [120]. In preliminary data from CBT recipients with baseline HADS anxiety subscale scores ≥8, the SD for the HADS anxiety subscale score was 4.2 at week 8 [110]. In addition, in a large acupuncture trial of cancer survivors, among 159 patients with baseline HADS anxiety subscale scores ≥8, the HADS anxiety subscale score SD was 4.0 during follow-up [155,156]. On the basis of these studies, it is assumed that the HADS anxiety subscale score SD will be approximately 4.2. Dividing the raw-score MCID of 1.7 points by 4.2 yields a standardized difference, that is, Cohen *d*=0.40. The noninferiority margin of Cohen *d*=0.35 SD is smaller than the standardized MCID (Cohen *d*=0.40) of the HADS anxiety subscale; as such, the noninferiority margin and statistical approach will find MT to be noninferior to CBT only if MT is not meaningfully worse than CBT.

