## Discussion

Cancer survivors represent one of the fastest growing populations in the United States [1]. Unfortunately, nearly 1 in 3 survivors experience anxiety symptoms as a long-term consequence of cancer and its treatment [3,5-9]. Although pharmacological treatment options are available, polypharmacy has become a growing concern for cancer survivors [28-31]. CBT is an established first-line treatment for anxiety [32,33,159], but not all individuals respond or wish to use CBT [45,47-49]. Although MT has a growing evidence base for anxiety in cancer populations [72-75], it remains unclear how MT compares with CBT as a treatment alternative. The MELODY study will address this evidence gap by determining the comparative effectiveness of telehealth-based MT and telehealth-based CBT for anxiety in cancer survivors. This study will intentionally support enrollment access for racially and ethnically diverse populations of English- or Spanish-speaking survivors from urban, suburban, and rural settings to improve the generalizability of the findings and to inform future efforts to reduce the disparities in survivorship care. By focusing on telehealth-based interventions, this study will capitalize on the accelerating digital trends in health care and society at large, helping patients and clinicians to navigate a growing array of remotely delivered care options.

Despite its novelty and strengths, the MELODY study has some limitations. First, the study lacks a usual care or waitlist control group and therefore cannot control for Hawthorne effects or regression to the mean; however, both MT [72-75] and CBT [40,43,160] have demonstrated effectiveness for anxiety symptoms in cancer populations. Second, although the study participants are screened for the presence of generalized anxiety disorder, they do not undergo a formal diagnostic interview for psychiatric disorders. Third, this study focuses on treating anxiety symptoms rather than an anxiety disorder. However, cancer care guidelines are often based on symptom severity rather than psychiatric diagnoses [161]. Furthermore, research indicates that anxiety symptoms are associated with poor quality of life and other problematic outcomes in cancer populations, even if symptoms do not meet the criteria for an anxiety disorder [23,162]. Thus, by focusing on symptoms, this study will align closely with clinical guidelines and enroll more patients who could potentially benefit from interventions.

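### Linking interview themes to change in HADS anxiety, with no account of baseline severity, can make a theme that tracks starting severity look linked to improvement

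*Protocol article*

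**What the plan says.** The section Qualitative Analyses ties themes to patient-reported outcomes in order to "explore whether specific themes vary according to the magnitude of change in the HADS anxiety score". It mentions no adjustment for, grouping by or display of baseline severity. On the order of work it says: "Interviews from each treatment arm will be analyzed separately and then compared for convergence and divergence".

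Other sections bear on this:

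- Eligibility Criteria requires a HADS anxiety score of at least 8, so people are selected on the outcome scale itself.
- Semistructured Interviews plans 30 purposively chosen interviewees per arm at week 8, "aiming for balance across age, sex, race, ethnicity, and treatment response". Baseline severity is not among these factors.
- The aims section gives the interviews exploratory standing: "Exploratory hypothesis: Survivors may have unique experiences with MT and CBT for anxiety during cancer survivorship".
- The Discussion grants that, with no usual care or waitlist group, the study "cannot control for Hawthorne effects or regression to the mean". This is stated for the trial as a whole and is not carried over to the theme analysis.
- The Aim 1 analysis works with change from baseline, and Sample Size and Power works with change scores. The article describes no baseline-adjusted HADS measure.

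**The concern.** Within an arm, people who voice a theme and people who do not form an observational contrast, and randomisation does not balance them. When entry depends on a high score, part of that score is short-term fluctuation, which tends to fall back at follow-up. Higher starters therefore tend to show larger drops. If what people say in interviews also varies with how anxious they were at the start, observed change mixes two things: whether an experience goes with benefit, and whether the person started high.

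What is at stake is interpretation. A reader could take a theme that goes with larger change as a clue to who benefits, particularly as the same section uses themes to supplement the heterogeneity analyses. If the treatment response used to choose interviewees is itself HADS change, the same dependence enters the sampling.

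**Working it through.** **The plan's own figure.** The article gives no figure for the theme analysis. Its nearest figure, 80% power for each primary test, reproduces: with 150 × 0.85 = 127.5 per arm, a margin of 0.35 SD and one-sided 0.025, the normal approximation gives 79.6% at 127 and 80.0% at 128 per arm. Nothing below depends on it.

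**Inputs from the article.** Follow-up SD s1 = 4.2 (Sample Size and Power: "it is assumed that the HADS anxiety subscale score SD will be approximately 4.2"); minimal clinically important difference 1.7 (Anxiety: "Research has identified a minimal clinically important difference (MCID) of 1.7 points"); entry at 8 or more; 30 interviewees per arm.

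**Inputs not in the article, assumed and varied.** The baseline SD s0 among those enrolled, the baseline to follow-up correlation r, and how strongly a theme tracks severity.

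**Step 1: does improvement depend on baseline?** With improvement = baseline − follow-up:

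- slope on baseline = 1 − r·s1/s0
- correlation with baseline = (s0 − r·s1) / √(s0² + s1² − 2·r·s0·s1)

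Example with s0 = 3.0 and r = 0.5: slope = 1 − 0.5 × 4.2/3.0 = 0.30; correlation = (3.0 − 2.1)/√(9 + 17.64 − 12.6) = 0.9/3.75 = 0.24. Correlations over a grid:

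| s0 | r=0.3 | r=0.4 | r=0.5 | r=0.6 | r=0.7 |
|---|---|---|---|---|---|
| 2.5 | 0.30 | 0.21 | 0.11 | −0.01 | −0.15 |
| 3.0 | 0.40 | 0.32 | 0.24 | 0.14 | 0.02 |
| 3.5 | 0.49 | 0.43 | 0.36 | 0.28 | 0.18 |
| 4.2 | 0.59 | 0.55 | 0.50 | 0.45 | 0.39 |

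The dependence vanishes where r = s0/s1 (2.5/4.2 = 0.60) and reverses beyond that. Over most of the grid it is positive.

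**Step 2: what would a theme comparison show?** A simulation drew baseline scores with mean 8 or 10 and SD 4.2 before selection, and follow-up scores with a mean 2 points lower, the same SD and correlation r. Scores were rounded and held to 0 to 21, and only baselines of 8 or more were kept. A theme with no effect on response was given to 70% of those above the median baseline and 30% of the rest.

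| Mean before selection | r | Baseline SD after cut | Correlation of improvement with baseline | Extra improvement, above-median starters | Theme difference | Theme difference, baseline-adjusted |
|---|---|---|---|---|---|---|
| 8 | 0.4 | 2.61 | 0.39 | 2.74 | 1.03 | −0.012 |
| 8 | 0.5 | 2.62 | 0.35 | 2.29 | 0.87 | 0.001 |
| 8 | 0.6 | 2.61 | 0.30 | 1.82 | 0.68 | −0.012 |
| 8 | 0.7 | 2.61 | 0.25 | 1.36 | 0.52 | 0.010 |
| 10 | 0.4 | 2.98 | 0.43 | 2.94 | 1.17 | −0.003 |
| 10 | 0.5 | 2.98 | 0.38 | 2.44 | 0.98 | 0.011 |
| 10 | 0.6 | 2.98 | 0.34 | 1.97 | 0.80 | 0.015 |
| 10 | 0.7 | 2.98 | 0.28 | 1.46 | 0.60 | 0.016 |

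Hand check: with an even split at the median, the theme difference should be about (0.70 − 0.30) = 0.40 times the severity difference. 0.40 × 2.94 = 1.18 against 1.17, and 0.40 × 1.36 = 0.54 against 0.52.

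**Step 3: how visible is it?** The theme differences are 0.17 to 0.28 SD of improvement. A two-sided 5% test would flag them in about 7% to 12% of comparisons of 15 v 15, and 10% to 19% of 30 v 30. No such test is planned; this only gauges how far the artefact would stand out at this sample size.

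**The case against.** The article says only that themes will be related to the size of change. It does not say raw change, and a condensed article may leave the exact measure to a fuller document. The work is exploratory and thematic, with no test, threshold or decision rule. Regression to the mean is openly conceded. Change from baseline is also the metric of the primary end points, so describing themes by it is consistent. The interview guide asks directly about perceived benefits and harms, so this link is not the only route from experience to benefit.

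All of that stands, and it keeps the point small. It does not remove it. The sentence names a measure, and since the article elsewhere uses change from baseline and change scores, unadjusted change is the natural reading. The Discussion's concession is not applied to themes. The shared entry rule helps comparisons between arms, not the pattern of themes against change within an arm.

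A reader might infer more: that higher starters must fall further whatever the therapy does, or that the artefact exceeds the minimal clinically important difference. The documents support neither. Suppose theme holders start 3 points higher. With s0 = 4.2 and r = 0.3 the slope is 0.70 and the artefact 0.70 × 3 = 2.1 points. But that needs a baseline spread as wide as the follow-up spread despite the entry cut-off, and a 3-point gap for which the article gives no basis. With s0 = 2.7 and r = 0.5 to 0.3 the slopes are 0.22 to 0.53, or 0.7 to 1.6 points, below 1.7.

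**Conclusion.** The point holds as a minor one. As described, the theme analysis takes no account of baseline severity, and in a sample selected on the outcome scale a theme that tracks severity can appear linked to improvement. A plausible size is 0.5 to 1.2 points. That range assumes correlations of 0.4 to 0.7 before selection, a pre-selection SD of 4.2 and a strong link between theme and severity (70% v 30%).

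The article gives none of the quantities that would settle the size, and with a low baseline SD and a high correlation the direction reverses. The simulated theme depends on the measured baseline score, which is why adjustment brings the difference to about zero. A theme tied instead to long-standing severity would behave differently, and adjustment alone might not remove the association.

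A reader might also infer that the trial's conclusions on MT against CBT are affected. They are not: the primary noninferiority tests do not use the themes.

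**What to change.** Add a sentence to Qualitative Analyses: when themes are linked to outcome, use a baseline-adjusted HADS anxiety measure alongside observed change, and show baseline HADS anxiety beside each theme. One suitable measure is each interviewee's residual from a regression of week 8 HADS anxiety on baseline HADS anxiety and arm, fitted in all trial participants. Reporting both measures lets a reader see whether a theme goes with improvement or only with a higher start.

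The cost is a small extra analysis and a measure that is less directly readable than a change in points, which is a reason to keep observed change beside it. Baseline and week 8 HADS are already collected (Table 1), so no extra interviews, participants or assessments are needed.
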